#### Secondary outcome

The secondary outcome variables in this study are:

*Change in the adolescent physical activity behaviour*. The physical activity questionnaire, for older children (PAQ-C), will be used to gauge the physical activity level of adolescents. The PAQ-C was applied for this study as it is deemed appropriate for schoolchildren aged between 8 and 14 years. This physical activity questionnaire, developed and validated by Kowalski [33, 34], is a self-supervised, 7-day questionnaire, that calculates moderate to healthy physical activity levels, during the school year [33, 34]. The personal administration of the questionnaire will be performed in a classroom. The PAQ-C holds ten items, with the score for each item ranging from 1 (low physical activity) to 5 (high physical activity), and the mean score for all items constitutes the overall PAQ-C score. To illustrate, item number 1 (rating 1 for ‘no’ and 5 for ‘7 times or more’) on the activity checklist, forms a composite score for item 1. Items from 2 to 8 (score 1 for the lowest, and 5 for the highest activity response) mean. It is essential that for item 9, the mean for all days of the week is taken into consideration, for a composite score (1 for ‘none’ and 5 for ‘very often’). Item 10 (PAQ-C) will not be contributed towards the final physical activity score. Its purpose is to identify students, who were unable to perform regular physical work during the week, due to illness or any other reasons. The mean score for the nine items constitutes the final PAQ-C activity summary score [34, 35]. According to Cronbach’s alpha r = 0.777 [36], the reliability of PAQ-C, in terms of physical activity level identification, is 0.777. A total mean score between 1 and 2.33 indicates a low level of physical activity, a mean score between 2.34 and 3.66 indicates a moderate level of physical activity, while a mean score between 3.67 and 5 indicates a high level of physical activity [37].

*Change in adolescent sedentary activity*. The adolescent sedentary activity questionnaire (ASAQ) will be used to determine sedentary time. The questionnaire queries participants, on the amount of time they spend in eleven different sedentary behaviours per day, during weekdays and during weekends. The questionnaire separates the sedentary behaviours into five categories: screen time (watching television, watching videos and DVDs, using a computer for entertainment, using an iPad or smartphone for entertainment, as well as playing video games such as Xbox, Wii, Nintendo, and PlayStation), education, (using the computer for studying, studying without using the computer and being tutored), travel (by car, bus or train), cultural activities (handicraft pastimes, hobbies or reading for recreation), social activities (chatting with friends, using a phone, chilling, and attending prayer sessions at the mosque). The total time for each activity of each category is first determined, followed by the calculation for total time of all categories, to determine the total sedentary time per weekday and per weekend [38]. A total time of (ASAQ) ≥ 4 hours/day is an indication of high sedentary behaviour, while a total time of < 4 hours/day is an indication of low sedentary behaviour [39]. The test-retest correlations are ≥ 0.70 [38].

*Change in food consumption frequency*. Semi-quantitative food-frequency questionnaire (SFFQ) will be used, to measure frequently consumed food items, in terms of time and total calories [40]. The SFFQ names 74 food items, and the categories for intake frequency are once per day, 2–3 times per day, 4–5 times per day, 6–7 times per day, 1–2 times per week, 3–4 times per week, 5–6 times per week, once a month, 2–3 times monthly, or never. The 74 items of nutrients, and the reproducibility rates of the food groups, are 0.46 and 0.49 respectively. Participants are queried on the type of food they consume, as well as the frequency of consumption and quantity [41].

*Change in the eating attitudes*. The eating attitudes test-26 (EAT-26) will be used, to collect data on the prevalence of eating disorders [42]. The eating attitude test is a 26-item questionnaire, widely applied to measure the symptoms and concerns, related to eating disorders in adults and adolescents, aged 13 years and above. The three main subscales of EAT-26 are dieting (13 items), bulimia as well as food preoccupation (6 items), and oral control (7 items). The dieting subscale questions include those associated to overweight anxiety, the desire to lose weight, vomiting, and the urge to vomit. The bulimia and food preoccupation subscale questions cover issues, associated to the persistent fixation over food. And the oral control subscale questions focus on the pressure, exerted by people in general, to be weight-conscious. Items are rated on a 6-point Likert scale ranging from ‘always’ (6), to ‘never’ (1). The six-point classification for the items from 1 to 25 extend from ‘always’ to ‘never’. A score of 3 is assigned for ‘always’, 2 for ‘usually’, 1 for ‘often’, and 0 for ‘sometimes’, ‘rarely’ and ‘never’. As for the 26^th^ item, a score of 0 is assigned for ‘always’, ‘usually’ and ‘often’, while a score of 1 is assigned for ‘sometimes’, 2 for ‘rarely’ and 3 for ‘never’. A score of 20 and above is indicative of an eating disorder [43]. The reliability of (EAT-26) is rated 0.87 by Cronbach’s α [44].

*Change in health beliefs*. Health belief will be measured by way of a self-report health belief questionnaire (HBQ). The breakdown of the 89 questions, representing eight perception and behavioural categories, are as follows: 13 questions on severity perception, separated into three subscales (emotional/mental health, physical health/fitness, and social/professional); 7 questions on susceptibility perception, separated into two subscales (lifestyle and environment); 14 questions on perceived barriers, separated into three subscales (practical concerns, emotional/mental health, and awareness); 13 questions on perceived benefits, separated into three subscales (emotional/ mental health, physical health/fitness, and social/professional); 12 questions on action cues, separated into two subscales (internal and exterior action cues); 18 questions on dietary self-efficacy, separated into two subscales (habits and preferences, and emotional/mental health); 7 questions on exercise self-efficacy, and five questions on weight management behavioural intention, separated into two subscales (dieting and exercising). All statements are rated by way of a five-point Likert scale, ranging from 1 (strongly disagree), to 5 (strongly agree). A higher score indicates a greater level of belief [45].

*Change in body mass index (BMI)*. The body mass index (BMI) will be reported in kg/m^2, by way of the formula BMI = kg/m2, in which kg is a person’s weight in kilograms, and m2 is his/her height in metres squared. Body weight will be measured using Omron HBF 375, to the nearest 0.1 kg. SECA body meter 206 will be employed to measure height, to the nearest 0.1 cm. Body mass index (BMI) will be classified into underweight, normal weight, overweight, and obese). A BMI less than 18.5 falls within the underweight range, a BMI of 18.5 to <25 falls within the healthy weight range, a BMI of 25.0 to <30 falls within the overweight range, and a BMI of 30.0 and above falls within the obese range. Additionally, the BMI-for-age (z-score) will be analysed using the WHO AnthroPlus version 1.0.4 software, while the WHO Growth Reference will be applied to categorise body weight status, using the reference data for children and adolescents aged 5–19 years.

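### The 4 hours/day sedentary split is set on the all-category ASAQ total, and the rule for non-normal data may make that split the tested outcome

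*Protocol article*

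**What the plan says.** In the Protocol article, under Secondary outcome (change in adolescent sedentary activity), pupils report time per day in eleven behaviours, for weekdays and for weekends. The behaviours fall into five categories. Besides screen time these are education ("using the computer for studying, studying without using the computer and being tutored"), travel and cultural activities ("travel (by car, bus or train), cultural activities (handicraft pastimes, hobbies or reading for recreation"), and social activities ("chatting with friends, using a phone, chilling, and attending prayer sessions at the mosque"). Time is totalled within each category first, "followed by the calculation for total time of all categories, to determine the total sedentary time per weekday and per weekend".

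The classification follows directly and refers to that total: "A total time of (ASAQ) ≥ 4 hours/day is an indication of high sedentary behaviour". Any total below that value counts as low. The cut is cited to a source and is not limited to any one category.

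The Statistical analysis section judges normality by a Kolmogorov-Smirnov test (P above 0.05 taken as normal) and by skewness and kurtosis between -1.96 and +1.96. It says non-normal data will be converted to a categorical variable. It then applies GEE to the selected outcomes without saying whether sedentary time enters as hours or as high/low.

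**The concern.** Each passage could be harmless alone. A high/low label used only to describe pupils does no damage, and a continuous total of sedentary time is a legitimate outcome. The difficulty lies in the combination. If sedentary time fails the normality test, the conversion rule applies, and the only categories the article supplies for the ASAQ are high and low at 4 hours/day.

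Two things would then be at stake:

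- **Meaning.** The tested class would depend on study, tutoring, travel, reading and prayer as much as on any other sitting. No teaching unit in the Intervention section or Table 1 aims to reduce these. More homework near an examination could move a pupil from low to high.
- **Power.** A pupil whose sitting time falls substantially without crossing 4 hours contributes nothing to a comparison of proportions. How much is lost depends on where the pupils lie relative to the cut.

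**Working it through.** The 4-hour cut is a cited threshold and not a calculated figure, so there is nothing to reproduce. The check asks how easily the cut is reached, whether the conversion rule is likely to apply, and what conversion would cost.

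**1. What 4 hours means on this total.** 4 h = 240 min. Over eleven behaviours this is 240/11 = 21.8 min each. Over five categories it is 240/5 = 48 min each. Two pupils with assumed times show how the class behaves:
- Total 3.5 h, plus 0.5 h extra homework: 3.5 + 0.5 = 4.0 h, so low becomes high.
- Total cut by 3 h, from 7.5 h to 4.5 h: (7.5 - 4.5)/7.5 = 40% less, and the pupil stays high.

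**2. Would the normality test fail?** The documents give no distribution. Assume lognormal totals with coefficient of variation (CV) 0.3 to 0.5. A Kolmogorov-Smirnov test with estimated mean and SD then rejects normality in about 87-100% of samples of 220-250 pupils. Without the correction for estimated parameters it rejects less often, most noticeably at CV 0.3.

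**3. Share classed high and power.** Inputs from the Sample size section: 220 pupils before attrition, so 110 per arm; design effect 2.2; effective n = 110/2.2 = 50 per arm. Assumed: mean total m, CV 0.3 or 0.5, a fall of 1 h/day, two-sided alpha 0.05.

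- Share high: 1 - Φ((ln 4 - μ)/s), with s² = ln(1 + CV²) and μ = ln m - s²/2.
- Power as hours: Φ(1/(SD·√(2/50)) - 1.96), with SD = CV × m in both arms.
- Power as high/low: Φ((d - 1.96·SE₀)/SE₁), where d is the difference in shares between means m and m - 1, SE₀ is pooled and SE₁ unpooled.

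Worked line, m = 7, CV 0.3:
- s = √ln(1.09) = 0.2936; ln 4 = 1.3863.
- Mean 7: μ = 1.9028, share = Φ(1.759) = 0.961. Mean 6: μ = 1.7487, share = Φ(1.234) = 0.891. Unrounded d = 0.0693.
- Hours: SD = 2.1, SE = 2.1 × √0.04 = 0.42, power = Φ(2.381 - 1.96) = 0.66.
- High/low: SE₀ = 0.0524, SE₁ = 0.0519, power = Φ((0.0693 - 0.1027)/0.0519) = 0.26.

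| Mean total (h/day) | Share high, CV 0.3 / 0.5 | Power, hours vs high/low, CV 0.3 | Power, hours vs high/low, CV 0.5 |
|---|---|---|---|
| 3 | 13% / 20% | 1.00 vs 0.70 | 0.92 vs 0.66 |
| 4 | 44% / 41% | 0.99 vs 0.94 | 0.71 vs 0.62 |
| 5 | 73% / 59% | 0.92 vs 0.84 | 0.52 vs 0.46 |
| 6 | 89% / 73% | 0.79 vs 0.54 | 0.38 vs 0.31 |
| 7 | 96% / 83% | 0.66 vs 0.26 | 0.30 vs 0.21 |
| 8 | 99% / 89% | 0.55 vs 0.12 | 0.24 vs 0.14 |

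An unpooled variance changes the high/low figures only slightly (0.87 instead of 0.84 at a mean of 5 h, 0.27 instead of 0.26 at 7 h, CV 0.3). Hours had the higher power in every row. These values serve to compare the two scales. They are not a forecast of the trial's power, because four schools bring small-cluster problems that are not modelled here.

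**The case against.** The strongest reply is that the article never says the high/low class is the analysed outcome. The heading speaks of change in sedentary activity, the ASAQ is there to determine time, and the cut is only called an indication. Friedman's test is also named for non-normal data. All of this is true, and it is why the split *may* become the tested outcome and not that it *will*. But Friedman's test is named only for within-group change over time, while the conversion rule is stated without exception and nothing exempts the ASAQ.

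A second reply is that the two normality criteria can disagree. For a lognormal, skewness is 3·CV + CV³: 0.93 at CV 0.3 and 1.63 at CV 0.5, both inside ±1.96 if the limits apply to the raw coefficient. Excess kurtosis, with w = 1 + CV², is w⁴ + 2w³ + 3w² - 6: 1.57 (inside) and 5.04 (outside). The article does not say which criterion governs. So at modest skew conversion might be avoided, but the outcome scale would then hang on an unstated choice.

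Three stronger readings are tempting, and the documents support none of them:
- *That the cut will label most pupils high.* This needs a mean the article does not give. At 3 h/day only 13-20% would be high.
- *That a two-day weekend sum is held against a per-day cut.* The text does derive a total "to determine the total sedentary time per weekday and per weekend", but pupils report time per day and the cut is in hours/day, so a per-day value for each day type is the natural reading. The missing rule for combining the two is detail that an article may leave to the full protocol.
- *That the split hides a fall in screen time, the programme's target.* No teaching unit names screen time. A fall can also change the class: with 2 h of other sitting, going from 3 h to 1 h of screen time moves the total from 5 h to 3 h.

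Whether the cited source set 4 hours for total or for screen time cannot be checked from the documents.

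**Conclusion.** The point holds in a limited form. The article does attach the 4 hours/day split to the total of all five ASAQ categories, and its rule for non-normal data can turn that split into the tested outcome. If that happens, the result can be driven by study or travel, and power is lost. In the illustration the loss is small when the mean total lies near 4 to 5 h/day (at CV 0.3, 0.99 to 0.94 and 0.92 to 0.84) and heavy at 7 to 8 h/day (0.66 to 0.26 and 0.55 to 0.12). At CV 0.5 power is lower on both scales and the gap narrower (0.30 to 0.21 at 7 h).

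These sizes rest on assumed lognormal times, a CV of 0.3 to 0.5, an assumed 1 h/day fall and 50 effective pupils per arm. The direction did not change anywhere in the range examined. This concerns one secondary outcome. It is a cheap improvement and does not threaten the primary result.

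**What to change.** Amend the ASAQ paragraph and the Statistical analysis section as follows:

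1. Analyse sedentary time as continuous hours per day in the GEE, with robust standard errors, or on a transformed scale if the skew requires it.
2. Exempt this outcome from the rule that converts non-normal data to categories.
3. State one day-weighted average of the weekday and weekend per-day values. With a five-day school week (an assumption to confirm) this is (5 × weekday + 2 × weekend)/7.
4. Report the category times already derived, with screen time shown separately. This is needed because a continuous total would still count extra study as more sedentary time.
5. Keep the 4-hour split, if wanted, as a descriptive percentage computed on the per-day value.

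The cost is text only, since every item is already collected. The downside is that a simple high/low percentage is no longer a tested result.

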## Abstract

**Background:**

Among the most urgent public health challenges, of the twenty-first century, is obesity. This can be attributed to its relationship with several non-communicable diseases (NCDs), as well as premature mortality. Being overweight or obese is a major concern not only in high-income countries, but also in low-income and middle-income countries, particularly in urban areas. Several studies have highlighted the prevalence of obesity, among Middle Eastern-descent adolescents, studying in Arabic secondary schools, located in Malaysia. Intervention studies, directed at Middle Eastern adolescents in Malaysia, are limited. This paper, describes the protocol, for an integrated health education intervention process. Titled ‘Healthy lifestyle’, it is a primary prevention process, aimed at curbing obesity and disordered eating, among Middle Eastern secondary school adolescents, aged 13–14 years old, residing in Malaysia.

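### EAT-26 is assigned to give the prevalence of eating disorders, but a score of 20 or more yields only a screen-positive proportion (secondary outcome, minor)

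*Protocol article*

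**What the plan says.** The protocol article lists six secondary outcomes. The fourth is headed "Change in the eating attitudes". Its paragraph makes these statements:

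- **Purpose:** the EAT-26 "will be used, to collect data on the prevalence of eating disorders".
- **What it measures:** the questionnaire is "widely applied to measure the symptoms and concerns, related to eating disorders in adults and adolescents".
- **Structure:** "dieting (13 items), bulimia as well as food preoccupation (6 items), and oral control (7 items".
- **Cut-off:** "A score of 20 and above is indicative of an eating disorder".
- **Support:** "The reliability of (EAT-26) is rated 0.87 by Cronbach"; this is the only performance figure given.

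Elsewhere the target is worded differently. The Abstract (Background) describes a programme "aimed at curbing obesity and disordered eating". The Abstract's Conclusions and the hypothesis in the last paragraph of the Discussion also speak of disordered eating. The Abstract (Methods and anticipated results) names the EAT-26 as the only eating-disorder instrument.

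The Statistical analysis section adds a general rule that variables that are not normally distributed will be turned into categorical ones. It does not say whether the EAT-26 is to be analysed as a score or as a proportion.

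**The concern.** One paragraph gives two different targets for the same instrument: attitudes, symptoms and concerns on one side, and how common a disorder is on the other. A self-report score with a cut-off can serve the first. It can serve the second only if the cut separates those with a disorder from those without one almost without error. Cronbach's alpha does not address that, because it describes how well the items hang together and not whether a score of 20 identifies a disorder.

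Two features of the plan give the wording consequences. First, the categorisation rule could make the 20-point cut the analysed quantity, since it is the only EAT-26 category the article defines. Second, the dieting subscale covers worry about overweight and wish to lose weight, and the teaching sessions deal with the dangers of overweight. If weight concern shifted in either direction, students could cross the cut, and under the present label this would be described in terms of eating disorders in 13- to 14-year-olds.

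**Working it through.** **Score range.** The subscales hold 13 + 6 + 7 = 26 items. Each scores at most 3, so the total runs from 0 to 26 × 3 = 78. The cut of 20 belongs to this 0–3 scoring. The paragraph also mentions response codes from 1 to 6, but on those the lowest possible total is 26 × 1 = 26, already above 20. The dieting subscale alone can give 13 × 3 = 39 points, so a student can pass 20 on it without any other item.

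**Could the cut become the outcome?** On every item three of the six responses score 0. A skewed score with many low values is therefore likely (an inference, not a statement in the article). Under the categorisation rule such a score would be grouped.

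**What the share at 20 or more estimates.** The article has no figure of its own to reproduce. Let p be the true prevalence, Se the sensitivity and Sp the specificity of the cut.

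- Flagged share = Se × p + (1 − Sp) × (1 − p)
- True cases among the flagged = Se × p / flagged share

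The flagged share equals p only when (1 − Sp)(1 − p) = (1 − Se)p, that is, when false positives and missed cases balance. With Se = 0.80 and p = 5%, this needs 1 − Sp = 0.20 × 0.05 / 0.95 = 0.0105, a specificity of about 98.9%. The article gives no p, Se or Sp.

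**Illustration.** All values of p, Se and Sp below are assumptions.

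| p | Se/Sp | Flagged share | True cases among flagged |
|---|---|---|---|
| 2% | 0.80/0.85 | 0.016 + 0.147 = 16.3% | 0.016/0.163 = 10% |
| 5% | 0.80/0.85 | 0.040 + 0.1425 = 18.3% | 0.040/0.1825 = 22% |
| 2% | 0.90/0.95 | 0.018 + 0.049 = 6.7% | 0.018/0.067 = 27% |
| 5% | 0.90/0.95 | 0.045 + 0.0475 = 9.3% | 0.045/0.0925 = 49% |

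The flagged share is thus 7–18%, against an assumed true prevalence of 2–5%. With wider assumptions (p from 1% to 10%, Se/Sp from 0.60/0.85 to 0.90/0.95), the flagged share is about 6–20% and true cases make up 4–67% of it. The size of the gap varies a great deal with the inputs, but in none of these cases does the flagged share equal p.

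**The case against.** The strongest reply is that this is one loose clause. The listed outcome is eating attitudes, and the aim, conclusions and hypothesis all say disordered eating. The wording on the cut is *indicative of*, which is compatible with screening. Support for the cut may lie in the cited sources, and the choice between score and proportion may be left to a fuller protocol or SAP. EAT-26 is one of six secondary outcomes, and the primary outcome is the KAP questionnaire.

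Most of this stands, and it keeps the point small. It does not remove it: the purpose clause names disorder prevalence outright, and an analysis plan built on this text would inherit the label.

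Three stronger readings are tempting and should not be drawn:

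- **The trial will claim a fall in eating disorders.** No passage plans such a conclusion.
- **Most flagged students will be false positives.** This depends wholly on assumed values. At 0.90/0.95, true cases exceed half of the flagged once p passes 0.05/0.95 = 5.3%.
- **A real change in disorders could not be seen.** If p = 2% were halved at 0.80/0.85, the flagged share would fall from 16.3% to 15.7%, a relative fall of 4%. If p = 5% were halved at 0.90/0.95, it would fall from 9.3% to 7.1%, or 23%. At p = 10% the fall reaches 31%. The change is diluted, by an amount the article does not let us fix.

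**Conclusion.** The point holds as a misnamed quantity in one secondary outcome. The article assigns to a symptom questionnaire a prevalence that the described design does not measure, and this conflicts with its own outcome title and stated aim. That conclusion rests on the article's wording alone. The numerical gap (7–18% flagged for a true 2–5%, with 10–49% of the flagged being true cases) illustrates assumed accuracy and prevalence and is not an estimate for this trial. Severity is minor: the primary outcome and the sample size are unaffected.

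**What to change.** 1. In the EAT-26 paragraph under Secondary outcome, replace the reference to eating-disorder prevalence with *disordered eating attitudes*, in line with the Abstract and Discussion.
2. State that the outcome is the between-arm difference in total EAT-26 score (0–78, on the 0–3 item scoring), so that the categorisation rule in Statistical analysis does not make the 20-point cut the outcome by default.
3. Report the proportion scoring 20 or more as a *positive screen*, not as the prevalence of eating disorders.

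The cost is the rewording of one outcome definition and one added sentence on its analysis. No new data, visits or participants are needed. The downside is a less striking secondary claim.

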### Study participants

The study participants will comprise Middle Eastern students in early adolescence, within the ages of 13 and 14 years, located in Arabic schools in the Klang Valley area. The inclusion criteria include Arabic students aged 13 to 14 years, with at least one parent consenting to their participation in this study. Students afflicted with illnesses such as asthma, diabetes, cancer, cardiovascular diseases, fractures, cirrhosis, or other diseases, as well as students exempted from physical activities due a medical condition, will be excluded from this investigation. The sampling unit will be represented by a randomly selected Arabic school Middle Eastern adolescent, who meets the inclusion and exclusion criteria set for this study.

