**where**:

Z_1-α/2 =_ Standard score for (1–0.025) = 1.96Z_1-β =_ Standard score (1–0.20) = 0.84 (80% power)P1 = The proportion of those overweight from control group (p1) = 27.6%P2 = The proportion of those overweight from Intervention group (p2) = 23.1%Intra-cluster correlation (*P*) = 0.05Number of individuals in each cluster (m)DE = Design Effect = 2.2

$$n=2.2\times (1.96+0.84)\;\frac{20.276(1-0.276)+0.231(1-0.23)}{(0.276-0.23)2}$$

Sample size = 220

Adding 15% to the number of subjects as attrition rate = 250

Therefore, the total sample size is 250 participants (125 participants for each group).

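### Weight status in 13–14-year-olds is categorised by two conflicting rules, fixed BMI cut-offs and the WHO Growth Reference, and the protocol does not say which one defines overweight or obesity

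*Protocol article*

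**What the plan says.** All the relevant text on classification is in one paragraph of the protocol article, under Study outcomes, Secondary outcome, Change in body mass index (BMI).

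- It opens with four named categories: "Body mass index (BMI) will be classified into underweight, normal weight, overweight, and obese".
- It defines them by fixed values in kg/m². At the lower end, "A BMI less than 18.5 falls within the underweight range, a BMI of 18.5 to <25 falls within the healthy weight range". At the upper end, "a BMI of 25.0 to <30 falls within the overweight range, and a BMI of 30.0 and above falls within the obese range". Age does not enter.
- It then adds, as a further step, that "the BMI-for-age (z-score) will be analysed using the WHO AnthroPlus version 1.0.4 software", and that "the WHO Growth Reference will be applied to categorise body weight status, using the reference data for children and adolescents aged 5–19 years". No z-score cut-offs are given.

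The population is set under Study participants: "The inclusion criteria include Arabic students aged 13 to 14 years".

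The Statistical analysis section does not mention weight-status categories. It does say that variables found not to be normally distributed will be turned into categorical ones.

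**The concern.** Two rules in the same paragraph each produce weight-status categories from the same measurement in the same pupils. One compares BMI with constants. The other compares it with a reference that depends on age. A pupil can therefore be of healthy weight under one rule and overweight under the other, and the protocol does not say which label counts.

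This is a stated conflict and not a detail left for a later document, because both rules are written as things that will be done. What is at stake is the meaning of any overweight or obesity percentage the trial reports. If BMI fails the planned normality check and is categorised, the result of that analysis is at stake too. Preventing obesity is the programme's declared aim in the Abstract, and body weight status appears in the study hypothesis in the Discussion, so such percentages are likely to be read closely.

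**Working it through.** No planned figure depends on this definition, so there is none to reproduce. The check sets the two rules side by side and traces where the categories are used.

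**Inputs**

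| Item | Fixed rule | WHO Growth Reference rule |
|---|---|---|
| Quantity classified | BMI in kg/m² | BMI-for-age |
| Cut-offs | 18.5, 25, 30 | not stated |
| Age term | none | yes, reference data for ages 5–19 |
| Verb used | BMI will be classified | reference will be applied to categorise |
| Population | pupils aged 13 to 14 | the same pupils |

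**Step 1: can the rules agree?** Under the fixed rule a pupil is overweight or obese when BMI ≥ 25. Under an age-referenced rule, any z-score cut-off corresponds to a BMI value c(age), and the pupil is overweight or obese when BMI is beyond c(age). The rules give the same answer for every possible BMI only if c(age) = 25 at every age in the sample. A reference that moves with age cannot meet that condition throughout the age range.

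- Where c(age) < 25, pupils with BMI between c(age) and 25 are of healthy weight by the fixed rule and overweight by the WHO rule.
- Where c(age) > 25, the disagreement runs the other way.
- The same argument applies at 18.5 and at 30.

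This rests on age alone. The paragraph does not mention sex, and the point does not need it.

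**Step 2: is there a rule of precedence?** The BMI paragraph links the two with a word meaning in addition, which does not rank them. The Statistical analysis section names neither rule. The Sample size section works from proportions overweight taken from an earlier study ("The proportion of those overweight from control group (p1) = 27.6"%, against 23.1% for intervention) and does not say how overweight was defined there.

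**Step 3: which results are touched?**

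| Result | Affected? |
|---|---|
| Primary outcome (knowledge, attitude and practice questionnaire) | No |
| Continuous BMI, kg/m² | No |
| BMI-for-age z-score | No |
| Percentages underweight, healthy, overweight, obese | Yes |
| BMI analysed as a category after failing the normality check | Yes, if it happens |

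The last row arises because the only BMI categories in the protocol are these two sets. If the normality rule sends BMI into categories, the choice of set would be made after the data have been inspected.

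**Step 4: how large is the disagreement?** For the overweight boundary, with c(age) < 25, the share of pupils classified differently is P(c(age) ≤ BMI < 25). This needs the BMI distribution of the sample and the value of c(age). The document gives neither, so no figure follows from it.

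**The case against.** The strongest reply is that the conflict is narrow and partly resolved. The listed secondary outcome is change in BMI, reported in kg/m², and the z-score is also to be analysed. Neither depends on a category rule. The sentence on the WHO Growth Reference gives that reference the task of categorising weight status ("while the WHO Growth Reference will be applied to categorise body weight status"), so the fixed ranges could be read as describing raw BMI only. Alternatively, both classifications might be reported side by side.

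Much of this stands. The continuous measures are safe, and BMI is one of six secondary outcomes. It does not remove the conflict, because the fixed ranges are also introduced as a classification that will be made, with the usual weight-status labels. Reporting both would still give two overweight rates with no stated order.

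The categorical analysis is also only conditional. BMI may pass the normality check, and for within-group comparisons of non-normal data the same section offers Friedman's test.

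A further reply is that pupils age little during the study. Six weeks plus two months is about 1.5 + 2 = 3.5 months, so the fixed cut-offs affect the level of prevalence more than its change. That is fair, and it limits the point to classification without claiming a distorted trend.

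**Conclusion.** The point holds in a limited form. The protocol states two conflicting rules for weight status in 13–14-year-olds and ranks neither. The consequence is confined to weight-status percentages and to any categorical BMI analysis triggered by the normality rule. It is worth correcting because the correction is nearly free and removes a choice that could otherwise be made with the data in view.

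The documents do not support two stronger readings that a reader might infer.

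- **That the disagreement between the rules swamps the planned effect of 27.6% − 23.1% = 4.5 percentage points.** The documents contain no basis for a discordance rate. A shift in prevalence level is also a different quantity from a difference between arms: one rule applied to both arms moves both levels, and the effect on the contrast cannot be inferred from the size of that shift.
- **That the sample-size proportions are themselves misclassified.** They come from an earlier study whose definition of overweight is not given, and the calculation does not use the 18.5, 25 or 30 cut-offs.

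The conclusion assumes only that a BMI-for-age reference varies with age, as its name says. It rests on the article as shown. An unseen analysis plan might choose between the rules, but the article would still state both.

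**What to change.** 1. Delete the fixed 18.5/25/30 kg/m² categories from the BMI outcome. Keeping them labelled as descriptive would settle the precedence, but would still publish percentages that ignore age.
2. Name the WHO Growth Reference for ages 5–19 as the only classification for overweight and obesity percentages, and state the z-score cut-offs for each category.
3. Name the BMI-for-age z-score as the analysed BMI outcome.
4. In the Statistical analysis section, state that if BMI is ever categorised, these same WHO categories are used.

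The cost is a few sentences, to be settled before outcome data are examined. Weight and height are already measured, and the z-scores and the software that produces them are already planned. No new data, visits or participants are needed.
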